#### Hospital Anxiety and Depression Scale-Anxiety (HADS-A)

The level of anxiety will be measured with the Chinese version of the HADS-A [38], which is a seven-item self-report instrument including specific items that assess generalized anxiety including tension, worry, fear, panic, difficulties in relaxing, and restlessness [39]. The scores range from 0 to 21. The Chinese version of HADS-A was tested in 314 Chinese patients with heart disease. The result showed high internal consistency, with Cronbach’s alpha of 0.85 and test-retest reliability of 0.90, respectively [38]. This scale was also validated in the community samples and showed a close correlation with both the Hamilton Rating Scale of Depression and Anxiety (Pearson’s coefficient = 0.67 and 0.63, respectively) [40].

#### Brief Resilience Scale (BRS)

The level of resilience (the ability to bounce back or recover from stress) will be measured by the Chinese version of the BRS [41], which is a six-item, self-report, and five-point rating scale. The scores range from 6 to 30. The Chinese version of the BRS was tested in 349 Chinese undergraduate students. A factor analysis revealed that it contained six factors with a factor loading ranging from 0.68 to 0.91 [42]. The results showed acceptable levels of psychometric properties which included a high internal consistency Cronbach’s alpha of 0.76 [41].

#### Short-form 12-item health survey version 2 (SF-12v2)

The health-related quality of life will be measured by the Chinese version of the SF-12v2 [43], which is a 12-item, self-report, and five-point rating scale. The scores range from 0 to 100. Higher SF-12v2 scores indicate better health-related quality of life. The Chinese version of the SF-12v2 was tested in 2410 Chinese adults who were randomly selected from the general population of Hong Kong. The results showed acceptable levels of psychometric properties which included a high internal consistency Cronbach’s alpha of 0.70 and test-retest reliability of 0.7 [44].

#### Neuropsychiatric Inventory Questionnaire (NPI-Q)

The behavior and psychological symptoms of the care recipient will be measured with the Chinese version of the NPI-Q, which is used to evaluate the frequency, severity, and caregiver distress of 12 neuropsychiatric symptoms including delusions, hallucinations, agitation/aggression, dysphoria/depression, anxiety, euphoria/elation, apathy/indifference, disinhibition, irritability/lability, aberrant motor behaviors, night-time disturbances, and appetite/eating disturbances using a five-point rating scale [45]. The Chinese version of the NPI-Q was tested in 173 patients with cognitive impairment and the results showed acceptable levels of psychometric properties which included a high internal consistency Cronbach’s alpha of 0.76 and test-retest reliability of 0.99 [45].

#### Level of mindfulness

Since the primary objective of the modified MBCT program is to help the participants cultivate a mindfulness attitude, the level of mindfulness will be measured as the process indicator using the Chinese version of the Five Facets Mindfulness Questionnaire Short Form (FFMQ-SF) [46], which has been commonly used to measure mindful awareness in mindfulness studies [47]. It is a self-report questionnaire measuring the five facets of mindfulness which includes observing, describing, acting with awareness, nonjudging of and nonreactivity to inner experience (e.g., “I’m good at finding words to describe my feelings”). The higher the score, the higher level of mindfulness. The Chinese version of the FFMQ-SF was tested in community-dwelling Chinese adults (*n* = 230) and clinical patients with significant psychological distress (*n* = 156) [46]. The results showed good test-retest reliability of 0.82 and a high internal consistency Cronbach’s alpha 0.80 in the community and clinical samples [46].

The adherence rate and frequency of mindfulness practice will be assessed based on the participants’ attendance in the weekly mindfulness training sessions in the experimental group. Additionally, they will be instructed to record the frequency and duration of mindfulness practice at home during the previous week. They will also be asked to write down weekly mindfulness practice duration (hours) and rate their overall level of adherence to their practice regimen on a 10-point scale from 0 (non-compliance) to 10 (full compliance) based on the following question: ‘Did I comply with the practice regimen in the past 7 days?’. This information will be collected weekly after the mindfulness program and will continue to be collected bi-weekly during the follow-up period. The reasons for any drop-out of each participant will also be recorded.

### Data analysis plan

IBM SPSS 23.0 software will be used for the data analysis. The Kolmogorov–Simonov test will be used for checking normality. To ensure the similarity of the subjects in the two groups (modified MBCT and SIRE) at baseline, the demographics, adherence rate, frequency of mindfulness practice, and the outcome measurements will be compared by using a *t* test for continuous variables and a Chi-square test for categorical variables. Covariates will be controlled in the main analyses if a significant difference of variables is found at baseline. Both per-protocol (PP) and intention-to-treat (ITT) analyses will be performed. In the PP population, we will include the subjects who attend > 70% of the intervention sessions. A sensitivity test will be performed to compare the differences between the ITT and PP results. The aim of conducting both ITT and PP analyses is to uncover factors affecting the use and effectiveness of the modified MBCT, such as noncompliance and acceptability [48].

Descriptive statistic will be used to analyze the recruitment rate, attrition rate, duration, patterns, and consistency of the participants practicing mindfulness to indicate the acceptability of the MBCT. Mixed multivariate modeling (MANOVA) tests will be adopted to investigate the between-group effect (groups: modified MBCT and SIRE), the within-group effect (times: T0, T1, and T2), and the interaction time effect of group by time effect (group × time) on all of the outcome variables including PSS, HADS-A, CESD, ZBI, BRS, NPI-Q, and SF-12v2, and the process indicator (FFMQ). Correlation checking by Pearson’s product moment correlation of all the psychological outcomes including PSS, HADS-A, CESD, ZBI, BRS, NPI-Q, SF-12v2, and the process indicator (FFMQ) at baseline will be performed. If the correlation is too strong (Pearson’s *r* > 0.6), which may result in multicollinearity and violation of the assumption of mixed repeated MANOVA, then two-way repeated ANOVA and Bonferroni’s adjustments will be adopted to prevent a type I error [49]. Post-hoc pairwise comparisons using Tukey’s Honestly Significant Difference (HSD) will be performed to examine the significant difference in the outcomes.

The Pearson’s correlation coefficient (*r*) (or Spearman’s correlation coefficient, as appropriate) will be adopted for the following variables to examine their correlations:The FFMQ total score as the independent variable and the outcome measurements including mean scores of stress, depression, burden, and anxiety as the dependent variables.The subscale (each facet) of the FFMQ score as the independent variable and the outcome measurements including mean scores of stress, depression, burden, and anxiety as the dependent variables.The duration of mindfulness practice as the independent variable and the level of mindfulness as the dependent variable.

The degree and pattern of missing data will be analyzed using SPSS Statistics Missing Values. If the missing value is a small amount (< 20%) and randomly distributed, the last observation carried forward (LOCF) method will be adopted to replace the missing data [50, 51]. However, if the missing values are not randomly distributed, multiple imputations will be adopted. This will create several different plausible imputed datasets and the results obtained from each of the sets will be appropriately combined [52].

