### Sample selection criteria

The target population is the community-dwelling family caregivers of PWD. Inclusion criteria are as follows: 1) those aged 18 years or older; 2) blood or by-marriage relatives (e.g., spouses, siblings, children, and grandchildren) of a person who has been clinically diagnosed with dementia, regardless of its types, with these relatives taking on the caring responsibilities ranging from physical aids to emotional support in the form of transportation, financial assistance, personal hygiene, and decision-making; 3) providing most of the daily care and support for PWD (daily contact for at least 4 h); and 4) able to speak Cantonese (for understanding all the teaching materials and instructions).

Caregivers will be excluded if they: 1) are practicing or recently learned meditation, mindfulness activities, and/or relaxation training in the past 6 months; 2) are diagnosed with a mental disorder such as bipolar disorder, schizophrenia, dementia, or depression in an acute stage; 3) are taking anticonvulsants or any kind of psychotropic drugs starting within the past 4 weeks which could be regulated or adjusted during the intervention period and thus the mental state might not be stable during the study; and/or 4) are identified with self-reported suicidal thought or drug abuse in the past 6 months.

The family caregivers receiving different types of support (other than MBI) such as domestic helpers, respite care, old age placement, old age allowance, meal delivery, or other financial support from the government will not be excluded, but the information will be reflected in the demographic data.

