### Outcome measurement

A variety of outcomes (described below) will be measured at baseline (T0), immediately after the intervention (T1), and at 6-month follow-up (T2). The FFMQ will be measured in the intervention group only and the baseline measurement will be conducted at the end of the third session (the mid-point of the intervention) when they have learned most of the basic skill and principle of mindfulness [28], followed by measurement immediately after the intervention (T1) and at 6-month follow-up (T2). The previous study showed that the participants’ level of mindfulness started to increase after the mid-point of the intervention, and the remaining sessions after the mid-point will further help the participants to cultivate a mindfulness attitude [29]. All assessments will be carried out by independent outcomes assessors who will be blinded to the group assignments. Sociodemographic data of the subjects will be obtained at baseline (before randomization and within 2 weeks before the implementation of the intervention) to assess the comparability of the groups and thus external validity of the results. Information such as caregiver relationships, time of caring for PWD, employment status, use of caring service, and so on, will be obtained.

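### The baseline comparison that selects covariates for the main analysis includes adherence and mindfulness practice, which are post-randomisation, MBCT-arm measures, and for true baseline variables it lets chance choose the model

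*Protocol article*

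**What the plan says.** The Data analysis plan sets out a check of group similarity at baseline in which "the demographics, adherence rate, frequency of mindfulness practice, and the outcome measurements will be compared" by t test or chi-square test. It then gives the consequence: "Covariates will be controlled in the main analyses if a significant difference of variables is found at baseline".

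Four other places bear on what those variables are:

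- **Level of mindfulness.** Adherence and practice frequency are "assessed based on the participants’ attendance in the weekly mindfulness training sessions in the experimental group". Home-practice duration and self-rated compliance are added, and of these the section says "This information will be collected weekly after the mindfulness program and will continue to be collected bi-weekly during the follow-up period".
- **Sample selection criteria.** Caregivers are excluded if they "are practicing or recently learned meditation, mindfulness activities, and/or relaxation training in the past 6 months".
- **Outcome measurement.** Sociodemographic baseline data are taken before randomisation.
- **Randomization and blinding.** Allocation is 1:1 by computer-generated blocks.

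The main model, also in the Data analysis plan, is a group-by-time analysis with T0, T1 and T2 as the repeated responses.

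**The concern.** Two separate faults sit in one rule.

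First, two of the screened variables are not baseline variables. Time spent practising mindfulness is a consequence of being allocated to MBCT and part of how MBCT is meant to work. The Limitations section itself looks to mindfulness level to understand mediation. A main analysis that holds practice constant no longer estimates the effect of being assigned to MBCT, which is the trial's question.

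Second, in a randomised trial a significant difference in a true baseline variable is a chance event. A rule triggered by such differences leaves the content of the primary model to the observed data instead of to prognosis.

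**Working it through.** The covariate rule carries no figure of its own to reproduce, and the planned sample size does not depend on it. The check is therefore what the rule does under each way of applying it.

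**Step 1. Adherence and practice: three possible applications**

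(a) *Pre-randomisation values.* None are described, and the exclusion criterion implies practice near zero in both arms. There is no difference, so the rule does nothing.

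(b) *Post-randomisation values, SIRE missing.* There is no second sample, so the test cannot be run. A complete-case model that included the variable would drop the control arm.

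(c) *Post-randomisation values, SIRE coded zero.* Assume 50 per arm and weekly practice in MBCT with mean μ = 3 h and SD σ = 1.5. The standard error of the difference is 1.5/√50 = 0.212, so t = 3/0.212 ≈ 14. Even with SD equal to the mean, t = √50 ≈ 7. Practice is selected almost surely.

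**Step 2. Effect of adjustment under (c)**

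Because SIRE is constant at zero, the practice slope is estimated wholly within MBCT. The arm coefficient becomes the MBCT–SIRE difference extrapolated to zero practice.

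- Correlation of practice with arm: r = (μ/2)/√(σ²/2 + (μ/2)²) = 1.5/√(1.125 + 2.25) = 0.816
- Variance inflation: VIF = 1/(1 − r²) = 1 + μ²/(2σ²) = 1 + 9/4.5 = 3.0
- SE multiplier: √3.0 = 1.73

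The documents give no practice figures, so a range is needed. Only the ratio σ/μ matters:

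| σ/μ (assumed) | VIF | SE multiplier |
|---|---|---|
| 0.4 | 4.1 | 2.0 |
| 0.5 | 3.0 | 1.7 |
| 1.0 | 1.5 | 1.2 |

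A simulation of 4,000 trials shows the shift in the estimate. It took 50 per arm, a true effect of 0.4 SD (the protocol's planning value), an assumed baseline–outcome correlation of 0.5, and practice with mean 1 and SD 0.4 in MBCT and 0 in SIRE. Both models adjusted for baseline. Practice differed significantly in every simulated trial.

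| Share of effect through practice | Estimate without → with practice | SE | Power |
|---|---|---|---|
| None | −0.40 → −0.41 | 0.17 → 0.36 | 63% → 20% |
| Half | −0.40 → −0.21 | 0.17 → 0.36 | 64% → 9% |
| All | −0.40 → 0.00 | 0.18 → 0.36 | 61% → 5% |

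These power figures compare two models at one follow-up visit. They do not check the planned sample size.

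**Step 3. True baseline variables**

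With k independent tests at 5%, the chance of at least one false imbalance is 1 − 0.95^k:

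- k = 7 (the outcome scales named in the Data analysis plan): 30%
- k = 15 (assumed): 54%
- k = 20 (assumed): 64%

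The scales are likely to be correlated; the plan itself provides for r above 0.6. That would probably lower these figures.

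**Step 4. Role of baseline PSS**

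T0 is a response level, so the group-by-time contrast uses it as a change from baseline. With equal variances and baseline–follow-up correlation ρ, the change contrast has variance proportional to 2(1 − ρ), and analysis of covariance has variance proportional to 1 − ρ². The ratio is (1 − ρ²)/(2(1 − ρ)) = (1 + ρ)/2. At ρ = 0.5 this is 0.75 (25% lower), and at ρ = 0.7 it is 0.85 (15% lower). The values of ρ are assumptions.

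**The case against.** The strongest reply is that the trigger is a difference found at baseline. Read strictly, that excludes anything measured later, and a two-sample test on a variable recorded in one arm has nothing to compare. No section says SIRE participants will be scored zero. Elsewhere the protocol gives practice data a sensible place: descriptively for acceptability, and correlated with mindfulness level. The listing may be a drafting slip.

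This reply is right about what cannot be claimed. A reader might infer that the rule as written makes practice a covariate and so removes the treatment effect. The documents do not support that: it needs application (c), which is nowhere stated. But the same paragraph names both variables in the baseline comparison that the rule draws on, so the contradiction stands and an analyst would have to resolve it without guidance.

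For adherence, the reply has a further point. SIRE also has seven sessions at the same frequency, and the per-protocol set needs attendance above 70%, so attendance might be recorded in both arms and need not differ. It would still be post-randomisation, and the Level of mindfulness section defines adherence for the experimental arm.

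Two other inferences should be resisted. Adjusting for a chance imbalance in a true baseline variable does not remove or bias the treatment effect. Nor is baseline PSS left out of the analysis, since T0 is one of the modelled responses.

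**Conclusion.** The point holds in this form. The Data analysis plan puts two post-randomisation, MBCT-arm variables into a baseline comparison that feeds covariate selection for the main analysis, which contradicts the sections that define them.

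The serious consequence is conditional. If they are entered with SIRE at zero, selection is almost certain, the estimate loses whatever part of the effect runs through practice, and the SE rises 1.2- to 2.0-fold over the assumed range of σ/μ. If SIRE is left missing, the rule cannot be carried out. The practice distribution, the degree of mediation and the zero coding are all assumptions, so the sizes are illustrative.

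For true baseline variables the fault is milder: a data-driven primary model, with a chance of about 30% (seven scales) to 54% (an assumed 15 variables) of at least one false trigger under independence, and no bias from the adjustment itself.

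**What to change.** 1. Delete adherence rate and frequency of mindfulness practice from the baseline comparison, and state that no post-randomisation variable enters the primary model. The bar would also cover the FFMQ, whose so-called baseline is taken in the MBCT arm at the end of the third session.
2. Replace the significance trigger with a short list of covariates named in advance on prognostic grounds. Baseline characteristics can still be tabulated by arm.
3. Use adherence and practice data only in descriptive or within-MBCT process analyses, as the protocol already does elsewhere.
4. Optional, as a precision gain and not the correction of an error: prespecify baseline PSS, and each secondary outcome's own baseline, as a covariate with T1 and T2 as the response visits. Moving T0 out of the responses also prevents baseline PSS from serving as both covariate and response, which the present rule would allow if PSS happened to differ.

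The cost is analysis wording only. Baseline PSS and the other baseline scores are already collected, and no new data or participants are needed.

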### Sample size

The sample size estimation was based on the primary outcome (stress). In the previous systematic review, the effect size of the MBCT for stress reduction was found to have Cohen’s *d* of 0.57 immediately after the intervention [15]. However, the intervention protocol is further modified and its duration is shortened in this proposed study. A conservative effect size Cohen’s *d* of 0.4 was adopted to detect the mean difference in stress reduction between the intervention and control groups. Based on the power analysis using the software G***Power 3.1 on repeated-measures analysis of variance (ANOVA), a sample size of 84 participants will be needed to achieve 80% power at a two-sided 5% significance level. According to the results of the feasibility study in Hong Kong, an attrition rate of 4% was found [16]. By adopting a more conservative estimation of the attrition rate of about 10%, the estimated sample size is at least 100 for this proposed study, 50 per group.

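### Baseline PSS is an outcome level by default and becomes a covariate only if a significance test fires; pre-specified adjustment would be more precise at almost no cost

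*Protocol article*

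**What the plan says.** The Outcome measurement section states that the outcomes "will be measured at baseline (T0), immediately after the intervention (T1), and at 6-month follow-up (T2"), so a pre-treatment PSS is planned for every participant in both arms.

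For PSS and the secondary scales, the Data analysis plan names mixed MANOVA "tests will be adopted to investigate the between-group effect (groups: modified MBCT and SIRE"), together with "the within-group effect (times: T0, T1, and T2), and the interaction time effect of group by time effect (group × time"). If the outcomes correlate too strongly at baseline, a two-way repeated ANOVA with Bonferroni adjustment takes its place. In both models T0 is one of the three levels of time.

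The same section compares the arms at baseline, outcome scores included, by t test or chi-square test. A variable enters the main analysis as a covariate only when that comparison is significant.

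The Hypotheses section frames the primary question as a greater fall in stress at T1 and/or T2. The Sample size section adopts a Cohen's d "of 0.4 was adopted to detect the mean difference in stress reduction between the intervention and control groups" and concludes that "a sample size of 84 participants will be needed to achieve 80% power at a two-sided 5% significance level", using G*Power "on repeated-measures analysis of variance (ANOVA"). It then allows for an "attrition rate of about 10%, the estimated sample size is at least 100 for this proposed study, 50 per group".

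**The concern.** With T0 as an outcome level, the group × time effect compares changes from T0. That fixes the slope on baseline at 1 and carries the full visit-to-visit noise of T0 into the arm contrast. A model that conditions on T0 estimates the same between-arm difference under randomisation and lets the data set the slope, so its variance is smaller for any correlation below 1.

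The covariate rule rarely changes this. Under randomisation, a baseline test at 5% is significant for PSS in about 5% of trials, so about 95% of the time there is no conditioning on it. When the rule does fire, T0 PSS would be a response and a predictor in the same model, and the form of the primary analysis would depend on the data. The reason to adjust is that baseline PSS predicts later PSS, whether or not the arms happen to differ.

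The between-group effect in the same model averages T0, T1 and T2. The arms are equal in expectation at T0, so this average understates the effect after treatment.

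At stake are precision in a trial of 84 to 100 caregivers and the risk that the group main effect is read as the treatment effect.

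**Working it through.** **Inputs.** From the Sample size section: d = 0.4, two-sided 5%, 84 analysed (42 per arm), 100 randomised, about 10% attrition (100 × 0.9 = 90, or 45 per arm). The correlation ρ between PSS visits is not given. The only related figure is the test-retest coefficient of 0.85 in the PSS section, which is plausibly an upper limit for visits separated by a 10-week programme and a further 6 months. Assumed range: 0.3 to 0.85. Unless stated otherwise, d is in single-visit SD units and participants are independent.

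**The plan's own figure.** For 80% power with f = d/2 = 0.2, two groups and three measurements, the repeated-measures formulas give:
- between effect, λ = f²·N·m/(1+(m−1)ρ): N = 68 at ρ = 0, 82 at 0.1, 134 at 0.5;
- group × time, λ = f²·N·m/(1−ρ): N = 82 at ρ = 0, 42 at 0.5 (multivariate form: 84 and 44).

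The stated 84 is therefore not fixed by the stated inputs, and neither ρ nor the effect tested can be read back from it. This is why a range is shown below.

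**Arm difference at one visit.** Variance multipliers (single-visit variance = 1):
- change from T0: 2(1−ρ)
- adjusted for T0: 1−ρ²
- ratio: (1−ρ²)/[2(1−ρ)] = (1+ρ)/2

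At ρ = 0.5 these are 1.00, 0.75 and 0.75. Power from the non-central t, 42 per arm:

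| ρ | ratio | change score | baseline-adjusted | gain (points) |
|---|---|---|---|---|
| 0.3 | 0.65 | 33.4% | 47.6% | 14 |
| 0.5 | 0.75 | 44.1% | 55.2% | 11 |
| 0.7 | 0.85 | 64.8% | 71.8% | 7 |
| 0.85 | 0.925 | 91.1% | 93.0% | 2 |

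At ρ = 0.5, 45 per arm gives 46.7% vs 58.2%, and 50 per arm gives 50.8% vs 62.8%.

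**If d is in change-score units.** Suppose the stated 80% power belongs to a change-score test. The non-centrality, about 1.96 + 0.84 = 2.80, is divided by √((1+ρ)/2). At ρ = 0.5, 2.80/0.866 = 3.23, and Φ(3.23 − 1.96) is about 90%, a gain of 10 points.

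**Against the planned interaction test.** Take effects of 0, 0.4, 0.4 at T0, T1, T2 and equal correlations. The 2-df group × time test has λ = (n/2)·Σ(δⱼ−δ̄)²/(1−ρ), with n = 42 per arm. At ρ = 0.5 this is 21 × 0.1067/0.5 = 4.48.

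| ρ | group × time, 2 df | adjusted, T1 only | difference (points) |
|---|---|---|---|
| 0.3 | 33.5% | 47.6% | +14 |
| 0.5 | 45.1% | 55.2% | +10 |
| 0.7 | 67.7% | 71.8% | +4 |
| 0.85 | 93.9% | 93.0% | −1 |

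**Group main effect.** Under the same effects the three-visit mean difference is (0 + 0.4 + 0.4)/3 = 0.27, two thirds of 0.4 whatever ρ is. At ρ = 0.5 and 84 analysed its power is 32%. The mean of T1 and T2 alone has 55%, and that mean adjusted for T0 has 73%.

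**Clustering.** Both programmes run in groups of 15–20, and the Group size section cites a group effect of 7% of outcome variability. Assume 7% of the single-visit variance arises after baseline in both arms, with 17 per group. This adds 0.07 × 16 = 1.12 to each multiplier. At ρ = 0.5 they become 2.12 and 1.87. Then 0.4/√(2·2.12/42) = 1.26 and 0.4/√(2·1.87/42) = 1.34, giving about 24% and 27% power by normal approximation, a gain of 2 to 3 points.

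**The case against.** The strongest reply is that nothing here is invalid. The primary hypothesis concerns a greater reduction in stress, group × time tests exactly that, and under randomisation changes from T0 are unbiased on average. This stands: the issue with that test is efficiency.

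A reader might infer that baseline PSS can never be a covariate. The plan does not say so, because its conditional rule covers the outcome scores. What remains is that the rule is data-driven and seldom triggered.

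A reader might also infer a fixed loss of about 11 power points. The documents do not support one number. It needs ρ = 0.5, which the protocol does not give; it compares a T0-to-T1 change test, not the planned 2-df interaction; and it ignores delivery in groups. At ρ = 0.85 the T1 adjusted test is level with the interaction test or slightly behind it. The figures also take PSS alone at 5%, whereas the plan has a multivariate test with a Bonferroni fallback.

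Finally, the group main effect may be only a routine part of the ANOVA output. That is fair: no section makes it the basis for the conclusion on stress. But the plan lists it beside group × time without saying which one decides, so a guard against misreading is warranted.

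**Conclusion.** The point holds as a matter of precision and pre-specification. By default T0 PSS is an outcome level, and adjustment depends on a test that would fire in about 5% of randomised trials. For the arm difference at one visit, always adjusting multiplies the variance by (1+ρ)/2 relative to a change score. That is worth about 14 to 2 power points for assumed ρ from 0.3 to 0.85, given d = 0.4 in single-visit SD units, 84 analysed and independent participants. Clustering within delivery groups would reduce the gain.

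The one-third dilution of the group main effect needs no assumption about ρ, only a constant effect at T1 and T2. That effect should not be used as the treatment effect.

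The documents do not support a claim that the group × time test is biased or that the planned primary analysis is invalid. This is a worthwhile, inexpensive improvement to a valid plan.

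**What to change.** For PSS, make T1 and T2 the outcomes in a model with arm, visit, arm × visit, baseline PSS and baseline PSS × visit, and a within-person covariance. Baseline PSS is always in the model. Report the adjusted arm difference at T1 and at T2. A constrained longitudinal model with a common T0 mean is an acceptable alternative and keeps participants who have only a T0 value.

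Remove the significance trigger for baseline PSS, and state that the group effect averaged over T0, T1 and T2 is not the treatment effect. Treat HADS-A, CESD, ZBI, BRS, NPI-Q and SF-12v2 the same way, each with its own baseline. FFMQ is outside this change, since it is measured in the intervention arm only.

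The cost is wording and one or two degrees of freedom. The T0 scores are already planned in both arms, the SPSS mixed-model procedure can fit the model, and no extra participants or visits are needed.

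### FFMQ is entered in the two-arm group × time model and the baseline correlation check, but it is measured only in the MBCT arm and never at T0, so its group effects cannot be estimated

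*Protocol article*

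**What the plan says.** In the Data analysis plan, the mixed MANOVA examines "the between-group effect (groups: modified MBCT and SIRE"), "the within-group effect (times: T0, T1, and T2") and their interaction. The variables it covers are given as "on all of the outcome variables including PSS, HADS-A, CESD, ZBI, BRS, NPI-Q, and SF-12v2, and the process indicator (FFMQ"). The same paragraph puts FFMQ in a Pearson correlation check at baseline. If any correlation exceeds 0.6, the plan moves to two-way repeated ANOVA with Bonferroni adjustment.

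The Outcome measurement section states: "The FFMQ will be measured in the intervention group only and the baseline measurement will be conducted at the end of the third session". Its later readings are at T1 and T2.

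The missing-data paragraph has two branches. Last observation carried forward applies under the condition "If the missing value is a small amount (< 20%) and randomly distributed". Otherwise, "if the missing values are not randomly distributed, multiple imputations will be adopted". It does not say how to treat an instrument that one arm never receives.

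The Sample size section gives the allocation: "the estimated sample size is at least 100 for this proposed study, 50 per group".

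**The concern.** The two sections cannot both be carried out. A model with a two-level group factor needs FFMQ from both arms, and the data collection supplies it from one. A time factor starting at T0 needs a pre-intervention reading, and the first FFMQ reading comes after three sessions of training.

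Two things are at stake. The first is the process indicator itself: any reported group or group × time effect on mindfulness would have no control data behind it. The second is the primary outcome, because PSS is listed in the same model. If all eight variables form one dependent vector, caregivers without FFMQ have an incomplete vector, and every SIRE caregiver is in that position.

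**Working it through.** **Inputs from the protocol article.** Two arms of 50 (Sample size). Three occasions and eight variables, seven outcomes plus FFMQ (Data analysis plan). FFMQ in MBCT only, at end of session 3, T1 and T2 (Outcome measurement). The plan states no figure of its own on this point, so there is none to reproduce.

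**1. Data cells for FFMQ.**
- Values the model calls for: 2 × 3 × 50 = 300.
- Values collected, before any drop-out: 1 × 3 × 50 = 150, all in MBCT.
- Absent overall: 150/300 = 50%. Absent in SIRE: 150/150 = 100%.
- If the session 3 reading is not accepted as T0, 1 × 2 × 50 = 100 values fit the stated occasions, and 200/300 = 66.7% are absent.

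**2. Estimability for FFMQ alone.** Write the six cell means as μ(arm, time). The group effect at time t is μ(MBCT, t) − μ(SIRE, t). The interaction at T1 is [μ(MBCT, T1) − μ(MBCT, T0)] − [μ(SIRE, T1) − μ(SIRE, T0)]. Every such contrast contains a SIRE mean with no data. Even with the session 3 reading counted as T0, the design matrix has rank 3 of 6. Only the time course within MBCT can be estimated.

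**3. The joint model.** Eight variables at three occasions make 8 × 3 = 24 values per caregiver. A SIRE caregiver can supply at most 7 × 3 = 21. Complete cases are therefore at most 50 in MBCT and 0 in SIRE, and the group design has rank 1 of 2. Without FFMQ, 21 of 21 values are planned in both arms, giving up to 50 + 50 cases.

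**4. Do the plan's other provisions help?**
- *Two-way repeated ANOVA fallback.* Run per outcome, it restores SIRE data for PSS and the other six outcomes. FFMQ still has a single group level.
- *Trigger for the fallback.* The check uses FFMQ at baseline, but no T0 value exists in either arm. The only candidate is the session 3 reading in MBCT, taken later than the T0 values it would be correlated with.
- *Last observation carried forward.* It does not apply: at least 50% is absent against a limit of 20%, absence is determined by arm, and SIRE has no observation to carry.
- *Multiple imputation.* Read literally, this is the branch left. An imputation model for FFMQ can be fitted only in MBCT. With PSS as predictor and slope b, the imputed arm difference is b × (mean PSS in MBCT − mean PSS in SIRE), whatever the true SIRE level of mindfulness.

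**5. Illustration of the imputation route, with assumed inputs.** Slope −0.5, PSS lower by 0.4 SD in MBCT, 50 per arm, 5 imputations, 500 runs. The formula gives (−0.5) × (−0.4) = 0.20. The simulated estimates were 0.201, 0.198 and 0.189 for true FFMQ differences of 0.2, 0.7 and 1.2. The estimate does not track the truth. The value 0.20 is only the product of the assumed inputs and is not a prediction for this trial.

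**The case against.** Four arguments can be made for the plan.

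- *Values never scheduled are not missing.* The missing-data paragraph reads most naturally as a rule for incomplete follow-up, and the authors may not count values uncollected by design as missing. This stands. A reader might infer that the plan's own rule will manufacture control-arm mindfulness scores. The text permits that literal reading because it states no exception, but it does not direct it.
- *A simulated bias is not a trial quantity.* This stands too. With a correlation of −0.4 in place of the slope of −0.5, the imputed difference becomes 0.4 × 0.4 = 0.16 SD. Neither input is in the protocol, so no specific spurious effect can be attributed to the plan.
- *The stress comparison may be unharmed.* FFMQ is labelled separately as a process indicator, and the text does not expressly say that all eight variables form one dependent vector. If the fallback is triggered, PSS keeps its SIRE data. If the joint model is run on complete cases, the group term has no degrees of freedom and the failure is visible at once. A reader might infer that the primary analysis is certain to lose its control arm; that goes too far. Still, including FFMQ in a check meant to protect the MANOVA from multicollinearity makes sense only if FFMQ is one of its joint dependent variables, so the joint reading is the better supported one.
- *No hypothesis needs the contrast.* The between-group hypotheses cover stress and the secondary outcomes. The mindfulness hypotheses are correlations offered to explain change within MBCT, and they are planned separately. This is correct and limits the damage, but it does not make the stated model workable.

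None of these arguments resolves the conflict between the Outcome measurement section and the Data analysis plan.

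**Conclusion.** The plan is wrong as written. FFMQ has values for 0 of 50 SIRE caregivers and no true T0 value in either arm, so neither its group effect nor its group × time effect can be estimated by MANOVA or by the fallback ANOVA. This part rests only on the protocol's own statements.

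The consequence for stress is conditional. If FFMQ is a joint dependent variable and the MANOVA uses complete cases, all 50 SIRE caregivers drop out of the model that contains the primary outcome. Under that reading, the plan's only stated escape is the r > 0.6 fallback to separate ANOVAs. The primary comparison is unaffected once FFMQ is taken out.

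The consequence through imputation is a possibility only. If the multiple-imputation branch were applied to SIRE, the resulting FFMQ contrast would carry no information on that arm.

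**What to change.** - In the Data analysis plan, delete FFMQ from the variables in the group × time model and from the baseline correlation check.
- Analyse FFMQ within MBCT only, over end of session 3, T1 and T2, as process data. Keep the planned correlations of FFMQ with the outcomes and with practice duration, stated as MBCT-only.
- In the missing-data paragraph, state that FFMQ is not imputed for SIRE.
- In Limitations, restrict the wording about a mediating effect to association within MBCT. A series from one arm cannot show mediation of a between-arm effect.

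These are wording changes with no new data collection. The cost is that no between-arm or mediation claim on mindfulness can be made, and the data as planned cannot support one. Keeping FFMQ in the two-arm model would instead require measuring it in both arms at T0, T1 and T2. Recruitment began in May 2018, so a T0 reading can no longer be obtained for caregivers who have already started their sessions.
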